### Statistical analysis

The sample size calculation was based on an incidence of hospital admission of 40% and a reduction of 10% in the study group, a 2-year follow-up, and a 1:1 ratio for control and intervention groups. Under these constrains, a fixed alpha and beta errors of 5%, yielded an estimated size of 581 subjects per group. The statistical power of this sample, assuming alpha and beta errors of 5% was 85.3%.

All collected variables will be described for the overall study sample and for both study groups. Quantitative variables will be described as the mean and standard deviation (SD), and as the median and interquartile range (IR) for normally- and non-normally distributed variables, as confirmed by the Kolmogorov-Smirnov test. Categorical variables will be described as frequencies and percentages. Measures of central tendency will be compared using the T-test for independent samples or ANOVA, or their non-parametric counterparts: the Mann-Whitney U and Kruskal-Wallis tests. Categorical variables will be compared using the Chi-square test or Fisher’s exact test. If post hoc analyses are performed, the Bonferroni or the Games-Howell adjustments will be applied. Variables with differences in the bivariate analysis at baseline (*p* < 0.1) and those considered clinically relevant for the authors will be included in a linear multiple logistic regression to build a multivariate model to predict the difference in mean days of hospital stay and costs of patients in the HC program. To address Better Care and Better Health endpoints, the authors will apply a binary logistic regression for mortality and hospital admission variables; age, gender, and comorbidity burden will be included as adjustment variables. A backward stepwise regression will be used to avoid overfitting of the model obtained.

A significance threshold will be set at two-sided alpha value < 0.05. The analysis will be performed with SPSS (IBM Corp. Released 2012. IBM SPSS Statistics for Windows, Version 21.0. Armonk, NY: IBM Corp.).

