### Endpoints and variables

The primary endpoint will be the difference in mean days of hospital stay per year between patients included in the integrated and functional HC programs. Secondary endpoints will include the assessment of the differences between the two HC models i.e., mortality and hospital admissions, based on the IHI Triple Aim (Better Care, Better Health, Lower Costs) [26]. To this end, variables regarding subjects’ health status, quality of care, and resource utilization of patients included in the two models will be compared (Table 3). The demographic characteristics of the study participants will also be recorded.

**Table 3 Tab3:** Study variables

	Definition and Measurements	Categories
Demographic Characteristics		
Age	At the moment of entering the HC program	65–74 75–84 > 85
Gender		Male | Female
Health Status		
Caregiver	At the time of entering the HC program	Yes | No
Level of dependency	Scale defined by Royal Decree 174/2011; Law 39/2006 of Promotion of Personal Autonomy and Care for People in Situations of Dependency.	Grade I (25–49): Moderate dependency Grade II (50–74): Severe dependency Grade III (75–100): Great dependency
Decubitus ulcer	At physician’s discretion	Presence | absence
Drugs prescribed	By active substance.	Not polymedicated (< 5) Polymedicated (5–10) Hyperpolymedicated (> 10)
Comorbidity burden	Measured by Adjusted Morbidity Groups (GMA) risk assessment tool. GMA considers the type of disease (i.e. acute or chronic), number of systems affected, and complexity of each disease, which is coded by the International Classification of Diseases (ICD-9-CM) and stratify depending on the complexity.	31 qualitative ordinal GMA levels.
Mortality	Death during follow-up	Yes | No
Realization of CGA		Yes | No
Assessments included in CGA		
Performance of normal daily tasks	Barthel Scale [27]	Total dependency (< 20) Severe dependency (20–60) Moderate dependency (61–90) Mild dependency (91–99) Autonomous (100)
Mental health	Pfeiffer’s Test [28]	High risk (≤2) Mild cognitive impairment (3–4) Moderate cognitive impairment (5–7) Severe cognitive impairment
Decubitus ulceration risk	Braden Test [29]	High risk (< 12) Moderate risk (13–14) Low risk (15–18)
Social risk	TIRS [30]	There is social risk when one indicator over 6 is positive
Anxiety	Goldberg Scale [31]	Probable anxiety (≥4 positive responses) Probable depression (≥2 positive responses)
Geriatric depression scale	Yesavage Scale [32]	No depression (1) Possible depression (≥ 2)

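### The only sample-size and power calculation is for the proportion admitted to hospital, a secondary endpoint; the power for the primary endpoint, mean hospital days per year, is not given and is unknown

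*Protocol article*

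**What the plan says.** In the Endpoints and variables section, the article states: "The primary endpoint will be the difference in mean days of hospital stay per year between patients included in the integrated and functional HC programs". The same paragraph then lists what is secondary: "Secondary endpoints will include the assessment of the differences between the two HC models i.e., mortality and hospital admissions". Admission is thus secondary.

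Under Statistical analysis, the sizing paragraph starts: "The sample size calculation was based on an incidence of hospital admission of 40% and a reduction of 10% in the study group". It adds "a 2-year follow-up, and a 1:1 ratio for control and intervention groups", and concludes that "a fixed alpha and beta errors of 5%, yielded an estimated size of 581 subjects per group". The next sentence gives the power of that sample as 85.3%, again citing alpha and beta of 5%. The test level is two-sided 5%.

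Neither section gives a mean, an SD or a target difference for hospital days. For quantitative variables the article allows a t-test or ANOVA, or the Mann-Whitney or Kruskal-Wallis test. It also plans a multivariable model for the difference in mean days.

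**The concern.** A power figure is a property of one endpoint, one effect and one test. Here the figure printed for the study belongs to a yes/no outcome, while the conclusion will rest on a mean of days.

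The two behave differently. If most patients have no hospital days and the rest have stays of varying length, the spread of stays adds noise to the mean that the proportion does not carry. A reader of a null primary result would take the study to have had 85% to 95% power for it, and might read the result as showing that the two models are equivalent. No calculation in the article supports that reading.

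This is not a detail left to a fuller document. The article does state a sizing basis and a power, and ties them to a different endpoint from the primary one.

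**Working it through.** **Inputs from the article (Statistical analysis):** 40% admitted in the control group; a reduction of 10%, read as 10 points, so 30%; two-sided alpha 5%; beta 5%; 1:1 allocation; 581 per group.

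**Step 1: reproduce 581.** For two proportions with mean 0.35,

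n = [1.96 × √(2 × 0.35 × 0.65) + 1.645 × √(0.40 × 0.60 + 0.30 × 0.70)]² / 0.10² = 589 per group (rounded up).

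The unpooled version, (1.96 + 1.645)² × 0.45 / 0.01, gives 585. Both are close to 581. A relative reduction (40% to 36%) would need 3,824 per group, so the 10-point reading is the one that fits. The figure 581 is a size for the proportion admitted.

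**Step 2: power on that endpoint.** At 581 per group, 40% v 30% has power 94.8%. This agrees with beta 5% but not with the stated 85.3%, which would need about 411 per group.

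**Step 3: power for mean days.** The article gives no spread, so one must be assumed. Let a share p be admitted, and let days among the admitted have mean m and coefficient of variation (CV) c. Then

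- variance of days = m² × [p(1 + c²) − p²]
- difference in means = (0.40 − 0.30) × m = 0.10m, if length of stay is unchanged
- power = Φ(difference / SE − 1.96), with SE = √[(variance 1 + variance 2) / 581]

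The mean m cancels. Expressing days per year also cancels if all patients are followed for the same time.

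Example, c = 1.0: the variances are m² × (0.80 − 0.16) = 0.64m² and m² × (0.60 − 0.09) = 0.51m². SE = m × √(1.15 / 581) = 0.0445m. The ratio is 0.10 / 0.0445 = 2.25, and power = Φ(0.29) = 61%.

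| Assumed CV of days among the admitted | Power, stay unchanged | Power, stays also 10% shorter |
|---|---|---|
| 0 | 94.9% | – |
| 0.5 | 86% | 99% |
| 0.8 | 72% | 93% |
| 1.0 | 61% | 86% |
| 1.3 | 47% | 73% |
| 1.8 | 31% | 51% |

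In the right-hand column the difference is (0.40 − 0.30 × 0.9) × m = 0.13m, and the study-group variance is multiplied by 0.81. With stay unchanged, power drops below 85.3% once the CV exceeds about 0.52. Simulation with lognormal stays and a Welch t-test gave slightly higher values than the formula at the larger CVs (65% at CV 1.0; 43% at CV 1.5, against 40% by formula).

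**Step 4: the rank test.** In the stay-unchanged scenario, simulated Mann-Whitney power was 93% to 94% at CV 0.75 to 1.5. Two further simulations show what it responds to:

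- 40% v 30% admitted, with stays one-third longer in the study group so that mean days are equal (0.30 × 4/3 = 0.40): Mann-Whitney rejected in 71%, 77% and 80% of runs at CV 0.8, 1.0 and 1.3; Welch rejected in about 5%.
- 40% admitted in both groups, with stays 25% shorter in the study group: Mann-Whitney rejected in 22%, 18% and 15%.

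**The case against.** The strongest reply is that a low power for mean days cannot be shown from the article. That is correct. A reader might infer that 581 per group has much less than the stated power for the primary endpoint. That depends on a spread of stay and an effect on length of stay, and the article gives neither. At CV 0.5 power is 86%, above the stated 85.3%. If stays shorten by 10%, it is 93% at CV 0.8 and 86% at CV 1.0. The Background expects less use of healthcare resources in general, so unchanged stays are not the only reasonable scenario.

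A second reply is that normality would be rejected with so many zeros, which leads to the Mann-Whitney test, and that this test keeps about 93% power. A reader might otherwise infer that a true 10-point fall in admissions would often be missed; for the rank test that is wrong. But the rank test does not rescue the power statement. With this many zeros it mostly tests any admission, and it often rejects when mean days are equal. Its 93% is not power for a difference in means.

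Two further inferences go beyond the documents. One is a specific shortfall in enrolment: the article reports no number enrolled at either centre. The other is that admission should be made primary to fit the calculation. That would change the endpoint of a registered study already under way, and the mismatch does not require it.

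**Conclusion.** The point holds as a mismatch that needs no outside assumption: the power printed for the study belongs to a secondary endpoint, and power for the primary comparison is unknown. The statement is wrong as written if read as the power of the study.

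The possible size of the gap rests on assumptions: a 10-point fall in admission, 40% and 30% taken as the shares with any hospital days over follow-up (the article does not say whether they are annual), equal follow-up, and an assumed CV. With unchanged stays, power for a difference in means is below 95% for any spread of stay and between 86% and 31% for CV 0.5 to 1.8. Shorter stays raise it. Separately, 95% and 85.3% cannot both describe 581 per group for 40% v 30%; the recomputed value is 94.8%.

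**What to change.** In Statistical analysis:

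- State that the calculation and its power apply to the secondary endpoint of any hospital admission. Say that the reduction is 10 percentage points, if that is what was meant. Reconcile the 95% implied by beta with the 85.3%.
- For the primary endpoint, report the power or the detectable difference in mean hospital days per year at the number actually enrolled, using the mean and SD of hospital days from the centres' own records.
- Base that figure on a test or model that targets the difference in means, and name it as the primary comparison. As a guide, 581 per group detects a difference of (1.96 + 1.645) × √(2 / 581) = 0.21 SD with 95% power, or 0.18 SD with 85.3% power.

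The cost is a record query, one rewritten paragraph and, in all likelihood, a less favourable stated power. Enrolment and data collection do not change.

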In the last decade, various approaches to care delivery for older people have been proposed, yielding a repertoire of models that range from traditional primary care and total patient models to integrated care models [5–7]. As part of the services offered, home care (HC) programs are intended to provide health care to patients that are unable to go to a primary care center due to their medical condition or disability, thus improving their health and active independence and reducing hospitalizations [8–11]. Some of these HC programs prioritize continuity in the sense that the same medical professional team (i.e., physician and nurse) attends the patient both at home and at the primary care center. This model, often referred to as integrated HC, has the advantage of strengthening the relationship between patients and their healthcare provider but struggles with the staff’s overloaded schedule [12, 13]. Other extensively applied models are based on skilled HC teams dedicated solely to at-home interventions; this approach, known as functional HC, increases specialization of the HC team and reduces the overburden of health care professionals, but may hamper the cohesion of healthcare services [14–16]. These models were implemented with positive outcomes regarding patients’ quality of life and care delivery satisfaction. However, studies investigating the outcome of HC have yielded heterogenous results, which likely depend on multiple factors including population factors, program characteristics, and healthcare setting [15–17]. In fact, even healthcare environments were HC is well established as a reality for care of older and disabled people acknowledge that more in-depth analysis is needed to improve understanding of the role of HC in the future of health care delivery [18]. Taken together, this heterogeneity precludes the appraisal of the benefits and drawbacks of HC approach, often leading to inconclusive evidence [19].

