Catalonia is the most north-eastern region of Spain, with a population of over 7.5 million people, 19% of which is older than 65 years. Here, HC programs are highly implemented, with nearly 90% of primary care units using traditionally integrated HC approaches within each provision of healthcare service, that enroll a 5% of the population older than 65 years. However, a survey of primary care professionals involved in HC programs revealed important disadvantages of this model, such as a high burden of care, time constraints, low resources and lack of coordination with other levels of care as each of the services provides HC assistance besides their center-based duties [20]. The change from a traditional integrated HC model to a functional full-time HC is expected to result in better outcomes for patients (clinical and related to the attendance experience), increased satisfaction for the professionals involved, and less use of healthcare resources. However, there is little or no evidence regarding the benefits and drawbacks of the two models when operating in the same healthcare environment. This study aims to compare two HC programs for older people applied in Catalonia: a traditional integrated HC model provided by healthcare professionals of primary care units and a specific full-time unit of medical professionals based on a functional HC model.

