### Selection criteria

All patients aged over 65 years old and enrolled in the long-term HC program at any of the two participating primary care centers for at least 3 months will be considered for eligibility. Patients will be included irrespective of their cognitive status. Exclusion criteria include patients with a life expectancy of less than a month and patients with a score of 5 or more in the Pfeiffer’s test that does not have a full-time caregiver or that have a part-time one because a severe cognitive impairment is likely to interfere with the study procedure. Patients that are not registered as Badalona citizens will also be excluded because it is assumed they have temporary status, as well as patients included in a HC program due to their reduced mobility to reduce bias when measuring patient-requested interventions because they cannot easily reach the primary care center facility.

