### Patient recruitment

Between June and October 2018, all subjects included in the HC program at the two primary care centers that met the selection criteria were contacted by phone and offered to participate in the study. Patients willing to do so were scheduled a domiciliary visit to receive the study documents (i.e., the Patient Information Sheet and self-administered questionnaires/scales) and sign the informed consent themselves or, in case of cognitive impairment, their full-time caregivers.

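### On the article's own coverage and population figures, 581 patients per group appears out of reach, and the stated 85.3% power does not match 581 per group in any case.

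*Protocol article*

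**What the plan says.** The Statistical analysis section plans on "an incidence of hospital admission of 40% and a reduction of 10% in the study group". Patients are to be followed for two years, and the groups are to be of equal size. With alpha and beta errors both at 5%, this "yielded an estimated size of 581 subjects per group". The next sentence gives the power of that sample as 85.3%. The significance threshold is two-sided 5%.

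The source of patients is fixed under Patient recruitment, with a window that ran from June to October 2018. The article says there that "all subjects included in the HC program at the two primary care centers that met the selection criteria were contacted by phone". Selection criteria adds a minimum of three months in the programme and several exclusions, and consent was then required. The article describes no other centre and no later entry.

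Two other places bear on how many patients that could be. Table 2 gives 3,480 residents aged 65 or over at the integrated-care centre and 2,970 at the functional-care centre, from 2015 data. The Background describes home-care programmes in Catalonia as ones "that enroll a 5% of the population older than 65 years".

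**The concern.** The target is 2 × 581 = 1,162 patients, taken from a closed pool at two centres. The article's own coverage and population figures imply a pool of roughly a quarter of that. If they are even approximately right locally, the stated size was not reached, and the planned 1:1 ratio is also doubtful because the two populations differ.

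The stated power is a second difficulty. A beta error of 5% means 95% power, yet the next sentence gives 85.3% for the same sample, so the paragraph contradicts itself whatever was recruited.

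What is at stake is how the result is read. The Discussion expects important policy implications. A reader who takes 581 per group and 85.3% at face value would give a non-significant comparison more weight as evidence of similarity than a much smaller sample could support.

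**Working it through.** **Inputs.** Control admission rate 40%, reduction 10%, ratio 1:1, alpha and beta 5%, two-sided test, 581 per group and 85.3% power (Statistical analysis); 3,480 and 2,970 residents aged 65 or over (Table 2); 5% coverage (Background). I read the reduction as 10 percentage points (40% v 30%), because a relative 10% (40% v 36%) would need 3,824 per group.

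**Step 1: reproduce 581.** Pooled-variance z test:

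n = [1.96·√(2·0.35·0.65) + 1.645·√(0.40·0.60 + 0.30·0.70)]² / 0.10² = (1.322 + 1.103)² / 0.01 ≈ 589.

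The unpooled form gives (1.96 + 1.645)² × 0.45 / 0.01 ≈ 585. Both lie within about 1.5% of 581, so the stated size is reproduced at 95% power.

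**Step 2: check 85.3%.**

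Power = Φ[(|p1 − p2| − 1.96·SE0) / SE1], with SE0 = √[p̄(1 − p̄)(1/n1 + 1/n2)] and SE1 = √[p1(1 − p1)/n1 + p2(1 − p2)/n2].

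- At 581 per group, SE0 = 0.02798 and SE1 = 0.02783, so power = Φ(1.622) = 94.8%.
- The size that gives 85.3% is (1.322 + 1.049 × 0.6708)² / 0.01 ≈ 411 per group.

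**Step 3: size of the pool at 5% coverage.**

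- Integrated: 0.05 × 3,480 = 174. Functional: 0.05 × 2,970 = 148.5, about 149. Total about 323, against 1,162.
- Share of residents aged 65 or over needed to reach 581: 581/3,480 = 16.7% and 581/2,970 = 19.6%, which is 3.3 and 3.9 times the stated coverage.

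**Step 4: power for 40% v 30% at 174 and 149.** p̄ = (69.6 + 44.7)/323 = 0.354, SE0 = 0.05337, SE1 = 0.05281. Power = Φ[(0.10 − 0.1046)/0.05281] = Φ(−0.087) = 46.5%. The detectable difference from 40% is 14.6 points at 80% power, 15.6 at 85.3% and 18.4 at 95%.

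**Step 5: vary the assumption.** Local coverage is not given, so I let it range, with every enrolee eligible and consenting:

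| Coverage | Integrated / functional | Power |
|---|---|---|
| 5% | 174 / 149 | 46.5% |
| 7% | 244 / 208 | 60% |
| 10% | 348 / 297 | 76% |
| 12.8% | 445 / 380 | about 85.3% |
| 15% | 522 / 446 | 90% |

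Participation below 100% lowers these. At 5% coverage, 80% participation (139 / 119) gives 39% and 50% participation (87 / 74) gives 26%. Both participation rates are illustrative; the article states none.

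**The case against.** The strongest reply is that the 5% is not a count at either centre. It is a regional average, and the sentence attaches it to units running the integrated model, which the functional centre is not. The populations date from 2015 and recruitment from 2018. This stands. A reader might infer that the two centres cannot supply 581 each, or that power is below one half, as established facts. The documents support neither without the coverage assumption: power passes one half by 7% coverage and reaches 85.3% at about 12.8%, if nobody is excluded or refuses.

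It is also fair that 581 is not a miscalculation (step 1), and that the power figures belong to hospital admission, which Endpoints and variables lists as secondary. They do not carry over to mean days of hospital stay per year. A condensed article may leave enrolment counts to the full protocol, so their absence alone is no fault. Nor does the article say that it will read a non-significant result as equivalence; its abstract even calls the study a pilot.

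These points limit certainty but do not remove the conflict. Even at twice the stated coverage with full participation, the centres yield 348 and 297. Nothing in the article suggests coverage of three to four times its own figure, and exclusions and consent can only reduce the numbers. The 85.3% discrepancy is untouched by any of this.

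A reader might also count the reduced-mobility exclusion as further evidence of shortfall. The article removes "patients included in a HC program due to their reduced mobility to reduce bias when measuring patient-requested interventions", while the Background says "home care (HC) programs are intended to provide health care to patients that are unable to go to a primary care center". That tension is real, but the article does not say how many patients it affects, and it enters none of the figures above. It is a separate point.

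**Conclusion.** The concern holds in conditional form. If the regional 5% applies to both centres and the 2015 populations are roughly current, the pool is at most about 323 against 1,162, and power for admission 40% v 30% is about 46.5%. Across 5% to 15% coverage with full participation, power runs from 46.5% to 90%, and 581 at both centres is not reached anywhere in that range. The size therefore appears unattainable on the article's own figures, though this is not proven without the local enrolment counts.

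The second part needs no assumption about recruitment. With the 10-point reading that reproduces the sample size, 581 per group gives about 95% power, so 85.3% contradicts both the 581 and the 5% beta error.

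**What to change.** - Keep the calculation of 581 per group as the a priori target, name hospital admission as its endpoint, and correct the power to about 95%. If 85.3% came from other inputs, state them.
- Beside it, give the number enrolled at each centre when recruitment closed in October 2018, the actual ratio, and the power or detectable difference those numbers give, with the endpoint named.
- State that the primary result will be reported as an estimate with its confidence interval, and that a non-significant result will not be read as no difference.
- As a separate point, reconcile the reduced-mobility exclusion with the programme's purpose in the Background, the abstract's opening remark that preventive home visits suit patients with reduced mobility, and the abstract's statement that all enrolled patients over 65 are included.

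The cost is rewording and probably a less favourable power figure. No extra patients are needed.

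### The sample-size paragraph gives 581 per group two incompatible powers: 95% (beta 5%) and 85.3%

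*Protocol article*

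**What the plan says.** All the relevant text is in one short paragraph of the protocol article (Methods, Statistical analysis).

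- Effect: "an incidence of hospital admission of 40% and a reduction of 10% in the study group".
- Design: "a 2-year follow-up" and "a 1:1 ratio for control and intervention groups".
- Error rates and result: "a fixed alpha and beta errors of 5%, yielded an estimated size of 581 subjects per group".
- Power, in the next sentence: "The statistical power of this sample, assuming alpha and beta errors of 5% was 85.3" per cent.
- Sidedness is given only for the analysis, at the end of the section: "A significance threshold will be set at two-sided alpha value < 0.05".

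The paragraph gives no allowance for losses, no evaluable number below 581 and no second effect size. It does not say whether the 10% reduction is absolute or relative.

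**The concern.** Beta is the probability of missing the planned effect, and power is its complement. Sizing at beta 5% is sizing for 95% power. The last sentence of the paragraph assumes beta 5% again and reports a power that implies beta 14.7%, for what it calls the same sample. That is a contradiction by definition, before any formula is chosen.

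If the study finds no difference in admissions, a reader will ask how likely it was to miss the effect it was planned for. The paragraph answers both 5% and 14.7%, nearly a threefold difference (14.7 / 5 = 2.9). The loose wording of the effect adds to this: a fall from 40% to 30% and a fall from 40% to 36% are very different targets.

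**Working it through.** **Inputs**, all from the Statistical analysis section: control rate 0.40; study rate 0.30 if the reduction is absolute, 0.36 if relative; alpha 0.05, two-sided (taken from the analysis threshold); beta 0.05; 1:1 allocation; 581 per group. Normal quantiles: 1.960 for alpha, 1.645 for 95% power, 1.049 for 85.3% power.

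**Step 1. Reproduce the 581 (40% versus 30%, 95% power).**

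Unpooled: n = (z_alpha + z_beta)² × [p1(1−p1) + p2(1−p2)] / (p1−p2)²
= (1.960 + 1.645)² × (0.24 + 0.21) / 0.10²
= 12.995 × 0.45 / 0.01 = 584.8, so 585 per group.

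Pooled: n = [z_alpha √(2p̄(1−p̄)) + z_beta √(p1(1−p1) + p2(1−p2))]² / (p1−p2)², with p̄ = 0.35
= [1.960 × 0.6745 + 1.645 × 0.6708]² / 0.01 = 588.3, so 589 per group.

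The arcsine formula also gives 589, and a continuity correction gives 609. A log-rank calculation with hazard ratio ln 0.7 / ln 0.6 = 0.698 needs 403 (Schoenfeld) to 412 (Freedman) events. Divided by 0.40 + 0.30, that is 576 to 589 per group. The 581 therefore agrees with its own inputs to within about 1% by the uncorrected formulas, though none returns it exactly.

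**Step 2. Power at 581 per group (40% versus 30%).**

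Standard error under the null: √(0.455/581) = 0.02798. Under the alternative: √(0.45/581) = 0.02783.

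z = (0.10 − 1.960 × 0.02798) / 0.02783 = 1.622, so power = 94.8%.

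**Step 3. Sample size that 85.3% belongs to (40% versus 30%, two-sided).**

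Unpooled: (1.960 + 1.049)² × 0.45 / 0.01, giving 408.
Pooled: [1.960 × 0.6745 + 1.049 × 0.6708]² / 0.01, giving 411.

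Against 581 that is a shortfall of 1 − 411/581 = 29% to 1 − 408/581 = 30%.

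**Step 4. Can any other reading give 85.3%?**

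| Reading | Two-sided power | One-sided power |
|---|---|---|
| 581 per group, 40% v 30% | 94.8% | 97.4% |
| Same, continuity-corrected | 94.1% | 97.0% |
| 581 as the total, 40% v 30% | 71.6% | 81.2% |
| 581 per group, 40% v 36% (relative) | 28.9% | 40.5% |

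None comes near 85.3%. At 581 per group, two-sided, that power would need a study-group rate of about 31.5%, which the paragraph does not mention. Under the relative reading, 95% power would need 3,821 (unpooled) to 3,824 (pooled) per group.

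**The case against.** The contradiction itself cannot be argued away, but its weight can be questioned.

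- **The calculation is not for the primary endpoint.** It concerns the incidence of admission, whereas Endpoints and variables makes mean hospital days per year primary and admission secondary. Neither 95% nor 85.3% is the power of the primary comparison. This stands: correcting the figure settles the power for admissions only.
- **The effect can be inferred.** Since 581 fits 40% versus 30% and a relative reduction would need more than 3,800 per group, the absolute reading is clearly the intended one. This largely stands, but a reader should not have to redo the calculation to learn the target effect.
- **The error is harmless.** Under Patient recruitment, all eligible enrolled patients were contacted between June and October 2018, so the sentence did not govern enrolment. If 581 and 95% are right, 85.3% understates the planned power. Both points are fair, but they bear on consequence, not on correctness.
- **The 85.3% may describe an achieved or evaluable sample.** That is possible, since two fixed centres need not supply 581 each. But the text attaches the figure to the calculated sample and to beta 5%, and gives no other number. An analysis plan not shown here could explain where the figure came from; it could not make both statements true.

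**Conclusion.** The concern holds. The paragraph assigns the same 581 per group both 95% and 85.3% power, and 85.3% is the figure that does not fit. At 40% versus 30%, two-sided alpha 5% and 1:1 allocation, 581 per group gives 94.8%. A power of 85.3% corresponds to 408 to 411 per group.

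The contradiction between beta 5% and 85.3% needs no assumption. Identifying 85.3% as the wrong figure rests on the absolute reading of the reduction, which is the only one under which 581 agrees with its stated error rates. Under the relative reading both powers are wrong (28.9%). The origin of 85.3% cannot be determined from the document.

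**What to change.** Replace the two sentences with one consistent statement: admission 40% versus 30% (10 percentage points, absolute), two-sided alpha 5%, 1:1 allocation, 581 per group, power 95%. Delete the 85.3%.

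If the authors did mean 85.3% as the power after losses or for an achieved sample, they should report it separately with the number per group it belongs to (about 410 under these assumptions, roughly 30% below 581) and the reason for the difference. The sentence should also say that the calculation is for hospital admission.

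The cost is one corrected sentence. It needs no additional patients and no change to conduct or analysis.
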